#### Qualitative.

Analyses of the 160 transcripts (interviews with each of the 40 couples at two time points: immediately post-intervention and at 12 months) will use a thematic approach to coding and summarizing using Dedoose qualitative analysis software [113]. A preliminary codebook will be developed from interview guides and rapid analysis content, then refined after all analysts code a set of transcripts independently and resolve discrepancies through consensus. The remaining transcripts will be single-coded, maintaining intercoder reliability of at least 80% throughout the coding process using kappa calculations. Coding memos will be used to summarize and explore the relationship between the constructs of the theory of change framework (e.g., the relationship between intervention processes and hypothesized mechanisms of change, or between mechanisms of change and outcomes). Analysts will also review and analyze coded serial IDI content within each participant’s dataset to look specifically for patterns over time to further understand sustained results.

#### Triangulation of quantitative and qualitative data.

Differences and similarities in the qualitative and quantitative data sets will be triangulated to build a more comprehensive understanding of how the hypothesized changes in mechanisms of action resulted in the intended outcomes and their relative weight in creating change among intervention participants. Both will be examined and presented to understand the relationship between the constructs in the conceptual model and to highlight any factors that may be uniquely identified. These data will inform interpretation of the efficacy findings and next steps for any refinements that may be necessary as the intervention is scaled up.

### Ethics approval

This study was approved by the Institutional Ethics Committee at St. John’s Medical College (IEC/1/829/2021) and the Institutional Review Board at the University of California San Francisco (Protocol 21–34788). All study materials and protocols have been reviewed by corresponding ethics boards in both English and Kannada. The study was approved by the Health Ministry Screening Committee (HMSC), the Indian Council of Medical Research, and the Ministry of Health, Government of India.

### Trial status

The study is currently active and enrolling. Recruitment was initiated in July 2023 and expected to conclude by September 2026. All assessments are anticipated to be completed by May 2027. After final data analysis and the writing of the results, we plan to share the main findings in manuscripts submitted beginning December 2027.

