Research staff will screen and obtain informed consent with the spouses separately. Due to varying literacy levels, the informed consent form will be read aloud to the participant. The participant will be asked to narrate back to the staff what they understand and is offered opportunities to ask questions. The participant will then insert their signature or their thumbprint on the form in the presence of an adult witness, followed by the obtaining of the signature or thumbprint of the adult witness. Following informed consent to participate in the study, the staff will enroll eligible couples in the study, conduct baseline assessments and randomly assign them to the intervention or enhanced usual care arm, as shown in Fig 3.

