### Data collection

Data collection will take place in person at five timepoints: baseline (pre-intervention) and three-, six-, nine-, and 12-month follow-up. Study staff will solicit support from ASHAs, PHC medical officers, and community-based non-governmental organizations who work with women and are well-known to PHC staff. After informed consent, research staff will administer baseline questionnaires using REDCap on study tablets. The husband will receive a reminder via text message to use the breathalyzer every day and to send a photo using it the subsequent week. At all remaining quarterly follow-up outcome assessments, the seven-day breathalyzer assessment will precede questionnaire administration. Breathalyzers will be dropped off and collected by members of the assessment team.

To assess the hypothesized mediators and mechanisms of change, IDIs will be conducted with the qualitative subsample at two time points: within three months after the end of the intervention and upon completion of the 12-month follow-up. Spouses will be interviewed separately by trained qualitative interviewers, with interviews audio-recorded, transcribed in the local language (Kannada), and translated to English for analyses.

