### Data analysis

#### Quantitative.

We will perform intention-to-treat (ITT) analyses to compare the treatment and control groups on the two primary outcomes: 1) mean overall AUDIT score as the measure of alcohol use; and 2) mean overall IFVCS score as the measure of IPV. We hypothesize that the treatment group will show a lower mean AUDIT score and a lower mean IFVCS score than the control group participants at 12-month follow-up. We will analyze this via a linear regression model for each outcome, in which we will control for the baseline outcome score and any relevant covariates for which the treatment groups might differ at baseline, despite randomization. A multilevel version of the models will be used for the longitudinal analyses, with repeated measures nested within participants and a random intercept for participants. The treatment arm*wave interaction will serve as the test of the intervention effect. Since each of these outcomes will only be collected from one of the spouses (alcohol use from the male and IPV from the female),combining/controlling for multiple reports within the couple is not necessary. If despite our extensive, proven-effective retention efforts, there is a substantial amount of missing data, we will use multiple imputations, assuming data are missing at random, including socio-demographic and other variables as auxiliary variables as appropriate, to perform sensitivity analyses of the original results [103].

Secondary analyses will consist of similar ITT linear regressions as for IFVCS above for the secondary outcomes of mean CPQ and breathalyzer scores. We hypothesize that post-intervention, the treatment group will show more positive and less negative communication patterns than the control group. We also expect that intervention participants will have lower post-intervention breathalyzer scores, on average, than the control group, reflecting reductions in frequency and quantity of alcohol use. Like the primary outcomes, the breathalyzer data is only available from one spouse, but CPQ data will be collected from both spouses. CPQ subscale scores will be constructed based on each spouse’s report separately, and agreement assessed via intraclass correlations. The treatment effect will be explored using husband and wife reports as the outcome variable in separate models to allow a differential effect of the treatment on mean CPQ subscale scores as reported by each partner in the couple [104].

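### The stated recruitment and assessment end dates are eight months apart and conflict with the 12-month primary endpoint

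*Protocol article*

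**What the plan says.** Three dates appear together under Trial status in the protocol article. On enrolment: "Recruitment was initiated in July 2023 and expected to conclude by September 2026". On follow-up: "All assessments are anticipated to be completed by May 2027". On reporting: "we plan to share the main findings in manuscripts submitted beginning December 2027".

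The visit schedule is the same for every couple. Data collection states: "Data collection will take place in person at five timepoints: baseline (pre-intervention) and three-, six-, nine-, and 12-month follow-up". The clock starts at enrolment, because under Recruitment & retention, after consent, "the staff will enroll eligible couples in the study, conduct baseline assessments and randomly assign them to the intervention or enhanced usual care arm".

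The primary comparison is made at the last of these visits. Under Data analysis (Quantitative), the treatment group is hypothesized to show "a lower mean AUDIT score and a lower mean IFVCS score than the control group participants at 12-month follow-up". Sample size determination also sets its power for an effect at 12 months: 320 couples with data, inflated to 400 for 20% attrition.

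The article gives no common closing date, no shortened follow-up for late enrolees and no earlier primary time point.

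**The concern.** A couple cannot reach a 12-month visit eight months after enrolment. Read together, the two dates leave the last few months of enrolees without the visit at which both primary outcomes are measured.

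The IFVCS would suffer more than the AUDIT. Table 2 schedules the IFVCS only at baseline, 6 and 12 months, so a late couple would contribute a single post-baseline value, at month 6. The AUDIT is quarterly, and some late couples would also have a month-9 value.

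The 20% allowance in the sample size is for attrition. Nothing in it covers visits that the calendar rules out. Two other elements depend on the month-12 visit: the second round of qualitative interviews and the sessions offered to control couples after their final assessment.

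**Working it through.** **Reproducing the plan's sample size.** Inputs from Sample size determination and Study design: alpha 0.05 (taken as two-sided), power 80%, SD 14, 1:1 allocation, 320 couples with data, 20% attrition.

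- Detectable effect with 160 per arm (normal approximation): (1.960 + 0.842) × √(2/160) = 0.313 SD, or 0.313 × 14 = 4.39 IFVCS points. This agrees with the stated d = 0.31 and lies within the expected 4 to 5 points.
- Enrolled number: 320 / 0.80 = 400, as stated.
- Power at exactly d = 0.31 with 320 couples is 79.2%. The stated 80% differs only by rounding of d.

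**Calendar, by month.**

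- September 2026 to May 2027 = 8 months. Shortfall = 12 − 8 = 4 months.
- A couple enrolled in September 2026 reaches month 12 in September 2027.
- To reach month 12 by May 2027, a couple must enrol by May 2026.
- June to September 2026 enrolees reach month 6 between December 2026 and March 2027, before the stated end. June to August enrolees reach month 9 between March and May 2027. September enrolees reach it in June 2027, after the stated end.

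**Calendar, by day.** The month names leave some room at each end.

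- Smallest gap: last enrolment 1 September 2026, last assessment 31 May 2027. Shortfall about 3 months.
- Largest gap: last enrolment 30 September 2026, last assessment at the start of May 2027. Shortfall about 5 months.

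No choice of days removes the shortfall.

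**Couples affected (illustration).** The article gives no accrual pattern. Assume 400 couples enrolled evenly from 1 July 2023.

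- Central case: 1 June to 30 September 2026 is 122 of 1,187 days (39 months). 400 × 122/1187 = 41 couples.
- Low: 400 × 93/1158 = 32 couples. High: 400 × 153/1187 = 52 couples.

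**Evaluable couples and power (illustration).** Apply the planned 20% attrition to the remaining couples. Power = Φ(d × √(n/2) − 1.960), with n per arm and no covariate adjustment.

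| Couples without month 12 | Evaluable | Missing at month 12 | Power at d = 0.31 |
|---|---|---|---|
| 0 (as planned) | 320 | 20% | 79% |
| 32 | 368 × 0.8 = 294 | 26% | 76% |
| 41 | 359 × 0.8 = 287 | 28% | 75% |
| 52 | 348 × 0.8 = 278 | 30% | 73% |

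In the central case the effect detectable with 80% power is 2.802 × √(4/287.2) = 0.331 SD, or 4.63 IFVCS points, against 4.39 as planned. Across the plan's own expected range, power moves from 72% to 68% at 4 points, from 82% to 78% at 4.5 points and from 89% to 86% at 5 points.

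**The case against.** The strongest reply is that these are forecasts in a status paragraph. Recruitment is expected, and assessments anticipated, to finish by certain months, and such wording sets an upper bound. Elsewhere the article schedules the 12-month visit for every couple without exception. Either date may simply be wrong: submitting manuscripts from December 2027 is still compatible with last visits in September 2027. This stands. A reader might infer that follow-up will be cut off in May 2027, so that the trial cannot deliver its primary endpoint for late enrolees. The article states no such cut-off, so that inference goes too far.

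A second reply is that the power figures overstate the harm. The planned regressions adjust for the baseline score, and if baseline and month-12 scores correlate at r, residual variance falls by the factor 1 − r². A correlation of √(1 − 287.2/320) = 0.32 would offset the drop from 320 to 287. The article gives no value for this correlation, so this is an assumption. Late couples' earlier visits would also contribute to the planned multilevel models. The detectable 4.63 points remains inside the expected 4 to 5, and power at 4 points was only 72% before any calendar loss. This stands as well: the figures do not establish an underpowered trial. Adjustment would, however, have helped the full 320 equally, so it offsets the lost information without restoring it.

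Neither reply reconciles the two dates. The conflict disappears only if enrolment ends by about May 2026 or assessments run to about September 2027, and the article says neither.

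**Conclusion.** The concern holds as a conflict of dates. The two stated end dates are 8 months apart, the endpoint needs 12, and the gap of about four months (3 to 5) follows from the article alone.

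The consequence is conditional on both dates being followed. In that case couples enrolled after about May 2026 would have no 12-month AUDIT or IFVCS. With even accrual and an unadjusted comparison, this is about 41 couples (32 to 52), about 287 evaluable instead of 320, and power of about 75% instead of about 80%. The loss is smaller with early-filling accrual or baseline adjustment, larger with back-loaded accrual, and nil if enrolment fills by about May 2026 or the May 2027 date is a misstatement.

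Because couples are randomized 1:1, truncation by calendar should fall on both arms alike. The expected harm is therefore lost information more than bias. The trial was still enrolling when the article was written, so the conflict can be settled before any visit is missed.

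**What to change.** Restate the dates under Trial status so that the last assessment falls at least 12 months plus the visit window after the last enrolment. There are two ways to do this:

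- Extend assessments to about September or October 2027. This costs some months of follow-up staffing and possibly later reporting, since December 2027 would leave little time for final analysis.
- Close enrolment by about May 2026. If fewer than 400 couples are enrolled by then, the sample size and power must be restated.

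In either case, add a sentence that every couple is followed to month 12 before the primary analysis, so that a calendar date does not decide who contributes to it. If May 2027 is a misprint, correcting it and adding that sentence is enough. No change to the design is needed.

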## Discussion

This manuscript outlines the protocol for a randomized controlled trial (RCT) of a couple’s intervention targeting co-occurring spousal alcohol use disorder (AUD) and intimate partner violence (IPV) for 400 couples, delivered by nurse-counselors in Bengaluru, India. The active condition consists of a 10-session, motivational interviewing (MI) and behavioral couples therapy (BCT) intervention delivered to 200 couples, while the control condition consists of a single session of enhanced usual care (n = 200 couples). A secondary aim consists of examining hypothesized mediators and moderators of intervention efficacy using quantitative and qualitative data.

The current Harmony intervention RCT has several strengths. First, it is among few programs that incorporate both partners in an IPV intervention. Many IPV interventions have focused on only women while AUD interventions have only targeted men. This separation places the entirety of burden to effect change in IPV on women who are already experiencing violence. Women-only interventions risk an IPV increase if the husband finds out that his wife has been accessing services for IPV. It is also important to include both partners when they have few options to leave and desire to stay together. Second, the intervention approach (i.e., working with both members of the couple and integrating the intervention into the public health care system) is novel and offers promising sustainability and scalability. Third, integration of BCT and MI will increase the evidence base of interventions for co-occurring AUD and IPV. Furthermore, intervention delivery by trained nurses increases scalability and addresses the ongoing treatment gap between the need for services and provider availability in South Asia and other resource-constrained settings worldwide. Additional strengths include use of an appropriately powered RCT to maximize internal validity, [114] use of culturally validated measures, and a study foundation from prior formative work [36] that found a similar intervention to be safe and acceptable.

Potential limitations and design considerations also accompany the study, including difficulties enrolling and retaining both partners in the intervention. To address this barrier, we have developed a plan to utilize ASHA community health workers who engage in a series of steps to re-engage families. The study team also has substantial experience with engaging vulnerable and marginalized participants in our previous trials in South India as well as in our pilot work [36,115,116]. In addition, the study may benefit from the positive focus on improving relationships and communication.

Like all intervention studies, ours includes potential risks, including the potential for the intervention to inadvertently increase IPV. However, our formative work with a similar population showed no safety concerns or increases in violence following participation [36]. A final risk is the time and cost burden on participants. We estimate the total time for the assessments in each wave to take between 60–90 minutes. Participants will be compensated for their time, transportation, and, if applicable, for lost wages when they miss work to attend sessions. To reduce the impact on the PHC staff, all assessments will be conducted by study interviewers and all intervention components are delivered by a study staff nurse-counselor with the same educational qualifications as the PHC nurses to ensure that the findings are generalizable.

## Conclusion

The Harmony study has potential to develop an evidence base for a novel, scalable, and sustainable intervention that combines MI and BCT to address concurrent AUD and IPV in primary care settings in India. Given that it is community based, it has the potential to be acceptable to couples who are otherwise unlikely to access services for IPV in situations in which few women have a real choice to leave an abusive relationship. If successful, this novel and combined intervention can be scaled up in community-based primary care settings as well as adapted to similar resource-constrained, global settings.
